### Intervention group – online MBSR for cancer (Mindfulness-based Cancer Recovery – MBCR)

Components of the MBCR program include: didactic instruction, experiential practice, and group process. Didactically, specific topics covered within the 2 hour sessions and in the participant manual are: (a) concepts fundamental to mindful living and mindfulness meditation, (b) emotional, behavioural and cognitive patterns, and how such patterns can influence individual stress responses, and (c) the physical and psychological symptoms of stress and the influence of stress on physical and psychological health. Participants are instructed to apply principles taught didactically, through experiential practice of mindfulness meditation during group sessions and also as homework between formal classes. Guided meditation recordings and videos are distributed to support home practice. Participants are expected to practice 45 minutes of meditation and yoga postures daily. During class sessions the instructor guides participants through experiential activities including gentle Hatha yoga, qigong mindful movement, and various types of mindfulness meditation such as sitting and walking meditations. The instructor facilitates group discussions to encourage conversation around challenges experienced with meditation practice. Both fellow participants and the instructor offer support and feedback to assist in problem solving when difficulties are encountered during meditation practice. The instructor encourages communication and support between group members to enhance the group process [12].

The online MBCR intervention was modeled after the F2F MBCR group intervention described above. The online format that most closely resembles F2F interaction (ability to see, hear and interact with group members in real time) is a synchronous online intervention with video and audio capabilities. In collaboration with the online education company eMindful Inc. (http://www.emindful.com), participants are able to access eMindful’s online virtual classroom and participate in real-time, online, synchronous, 2-hour MBCR classes for 8 consecutive weeks. Participants are asked to engage in the interactive features of the eMindful virtual classroom during the online classes. This includes logging on to the virtual classroom website, watching and listening in “real time” to streaming video and audio of the class instructor and other group participants on their computer screen, “chat” with the instructor and other group participants using a keyboard, and interactively participate using the headsets, web-cameras, and keyboards. Live images through the web-camera facilitate interaction with the instructor and other participants.

The virtual classroom allows for multiple webcams to be viewed by all participants and instructor simultaneously. Online classroom access requires a password and the instructor ensures only approved participants are present in the class. Recorded versions of the classes are available through software that prevents download of the recording (provided through streaming video) as well as password access. This classroom feature allows the PI to monitor MBCR treatment fidelity throughout the trial. Class content and schedule follow the adapted F2F MBCR manual utilized by both PI and Co-I (Drs. [name] and [name] respectively) and course program published elsewhere [37]. Participants are able to access the manual online or receive a hard copy from research coordinators through post if preferred. The guided meditation recordings and videos are available for participants to download electronically. Participants are provided both orientation/instructions for set up of the new equipment and also an orientation session before the first class where headsets, webcameras, website and classroom functionality are tested and reviewed. This orientation session is completed before the start of the first MBCR class. Each participant is emailed a summary of dates and orientation material before the start of session one. Technical support is continuously provided by eMindful during all online sessions to address any technical issues with the hardware and software, while study related questions are directed to the research coordinators.

### Treatment as Usual (TAU) wait-list control condition

In parallel with the online MBCR program, the TAU wait-list condition completes pre (T1) and post (T2) assessment measures before and after their wait period. Additionally, following the wait period, the control group completes the online MBCR intervention and completes one additional assessment time point (T3).

### Outcome measures and questionnaires

Table 1 contains the outcome measures and their administration timing for the online MBCR and wait-list group participants. Medical history (i.e., type of cancer, dates of diagnosis and treatment, and types of treatment received) and demographic information (i.e., sex, age, ethnic background, education, marital status, and current employment status) is obtained at the first assessment and later verified in the participant’s medical chart, with consent. Participants are also asked to indicate how much experience with meditation and/or yoga they have had previously.

**Table 1 T1:** Outcome measures for the online mbcr and wait-list group participants

***Construct***	***Measure***	***Administration***
Primary Objective: Feasibility	See Figure 1 for estimates –study deemed feasible if within 5% of each target value	
Program Satisfaction	eCALM –Online MBCR Program Evaluation Form	· Post intervention only
Dose of intervention delivered and dose received	Delivered: Attendance log Received: Meditation Log	· Throughout intervention
Distress Screening	Score of 4 or higher on the Distress Thermometer (DT)	· Pre intervention only
Primary Measure of Secondary Objective: Mood	Profile of Mood States (POMS)	· Pre and Post MBCR or wait
Other Secondary Outcomes: Stress	Calgary Symptoms of Stress Inventory (C-SOSI)	· Pre and Post MBCR or wait
Post-Traumatic Growth	Post-Traumatic Growth Inventory-Revised (PTGI-R)	· Pre and Post MBCR or wait
Mindfulness	Five Facet Mindfulness Questionnaire (FFMQ)	· Pre and Post MBCR or wait
Spiritualty	Functional Assessment of Chronic Illness Therapy-Spiritual Well-Being (FACIT-sp)	· Pre and Post MBCR or wait

### Meditation Log and attendance

Information on minutes spent in home practice of meditation and yoga is collected from each participant each week and returned to the study coordinator, which is shared with the group instructor. As part of the online virtual classroom capabilities, a basic feature of conference archiving is utilized. This feature can track all the MBCR classes with a list of attendees, and what time the participants entered and exited the classroom for attendance tracking.

### Screening measures

#### Distress thermometer

The Distress Thermometer (DT) is a 0 to 10 single visual analogue scale oriented as a vertical thermometer [38]. The DT has been validated against clinical diagnosis of anxiety and mood disorders, the Brief Symptom Inventory (BSI), the Hospital Anxiety Depression Scale (HADS), and endorsed for use by the National Comprehensive Cancer Network (NCCN). A cut-off score ≥ 4 has been identified in the literature as optimal with regards to both sensitivity and specificity for labeling individuals diagnosed with cancer as having significant psychological distress [39,40].

### Primary outcome measure

#### Profile of Mood States (POMS)

The POMS is an instrument with 65 items that assesses six affective dimensions and produces a Total Mood Disturbance (TMD) score [41]. Psychosocial interventions (including psychological adaptation to diagnosis and treatment of cancer) frequently use this scale. This instrument measures state (vs. trait) attributes, therefore the POMS scale is an appropriate instrument for repeated measures as previous administrations do not influence later administrations. The Kuder-Richardson overall internal consistency measure of the six subscales ranged from 0.84 (Confusion) to 0.95 (Depression) in two separate studies, with test retest stability ranging from 0.65 (vigor) to 0.74 (depression) over approximately a 20 day period. This is consistent with this particular instrument as a measure of mood states, which are expected to vary over time, and supports its construct validity.

### Secondary outcome measures

#### Calgary Symptoms of Stress Inventory (C-SOSI)

This measure is a 56-item scale and is a recent revision of the 95-item Symptom of Stress Inventory (SOSI) [42]. The original SOSI and the C-SOSI are both scales that are designed to measure multiple domains of symptoms of stress, including psychological and physical expressions of stress. The C-SOSI is the product of exploratory factor analysis on SOSI assessment data collected from individuals diagnosed with cancer who attended the Tom Baker Cancer Centre’s MBSR program [42]. A five-point scale (“never” to “very frequently”) is used to rate items based on frequency of stress-related symptoms during a specified time frame selected by the researcher (i.e., the past week). The C-SOSI items form 8 subscales: 1) Depression, 2) Anger, 3) Muscle Tension, 4) Cardiopulmonary Arousal, 5) Sympathetic Arousal, 6) Neurological/GI, 7) Cognitive Disorganization, and 8) Upper Respiratory symptoms. High internal consistency (0.80 to 0.95) has been demonstrated for both the total and subscale scores, as well as good convergent and divergent validity with other well-validated measures [40]. The original SOSI instrument has been used to measure change in symptoms of stress associated with MBSR participation in cancer populations [3,26,43].

#### Post-Traumatic Growth Inventory (PTGI)

This self-report scale is a 21-item inventory that measures the individual’s subjective perception of positive changes following adversity [44]. Individuals are asked to record, on a scale of 0 (not at all) to 6 (very great degree), the level to which their perspective changed as a result of their adversity. Reliability was 0.90 for the normative sample and 0.95 in a sample of individuals with cancer. The test–retest reliability that was measured in the normative sample 2 months later was 0.71.

#### Functional Assessment of Chronic Illness Therapy-Spiritual Well-Being (FACIT-Sp)

This scale is designed to measure spirituality in people with life threatening or chronic illnesses, and includes 12 questions that provide two subscales scores and an overall measure of spirituality [43]. The two subscales (meaning/peace and faith) correspond to one’s sense of meaning and/or purpose in life (e.g., My life lacks meaning and purpose) and one’s comfort and support from their personal faith (e.g., I receive support from my faith). The FACIT-Sp has been established as valid and reliable in individuals with cancer and HIV [44]. Cronbach’s alpha was 0.87 for the overall of spirituality, 0.88 for the faith subscale and 0.81 for the meaning/peace subscale [43].

#### Five Facet Mindfulness Questionnaire (FFMQ)

Baer and colleagues determined that the combined pool of 112 items from five separate mindfulness measures contain five interpretable facets of mindfulness [45]. The analysis revealed five factors that accounted for 33% of the variance. The five facets included in this measure of mindfulness are: attending to sensations, perceptions, thoughts and feelings; describing experience with words; acting with awareness; non-judging of experience; and non-reactivity to inner experience. The FFMQ showed incremental validity in predicting psychological symptoms and correlated strongly to conceptually related variables [45].

### Adverse events

All participants are requested to record and disclose any adverse events in their homework logs, and to report them to the group instructor or the research coordinators. The group instructor also inquires about the participants’ weekly experiences at each class session. Participants are welcomed and strongly encouraged to contact research staff to discuss any questions or events they consider problematic or issues for them regarding the study.

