### Screening, consent and enrollment

At first contact, interested participants are informed of the protocol and randomized design of the study. If interested, researchers ensure that individuals meet basic eligibility criteria. Potentially eligible participants complete the distress screen by phone conducted by the research coordinators. If interested and eligible, study procedures are explained in detail and consent obtained. Consent is also obtained to access medical records to confirm tumour location, stage and treatments received. Due to the lack of F2F contact during screening and consent, additional time is allocated to ensure fully informed consent by providing potential participants the opportunity to ask clarifying questions electronically or telephonically, and to require that the participant affirm that s/he has read the document, understands it, and has been presented with the opportunity to ask questions.

Researchers then provide a questionnaire package (including demographics and medical history, mood, stress, mindfulness, posttraumatic growth and spirituality measures) to complete online. Once a cohort is in place, participants are randomly allocated to one of two conditions using an online research randomization tool. All allocations are computer-based and not predictable. This process eliminates introduction of experimenter bias into participants’ group assignment. Once randomized participants are informed of group assignment (i.e., the immediate MBSR or the wait-list control condition) they are mailed a web-camera, headset, and MBSR course materials before they begin the program. Technical staff guide participants through installation of the equipment and online classroom tools in an orientation session before the first MBSR class. Those participants randomized to the wait-list condition are informed of their program start date and contacted closer to such date to send course materials.

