## Discussion

Recruitment for this trial has proceeded as anticipated; with participants arriving through the Alberta Cancer Registry via study invitation letters, through rural cancer centre posters, pamphlets, advertisements, and community-based networks. To date, 1800 individuals have been contacted through the Alberta Cancer Registry through mailed study invitation with 157 responding. Of those, 41 were ineligible (8 deceased, 3 outside of primary treatment inclusion criteria, 12 had scheduling conflicts, 9 had low distress, 6 had no computer/high speed Internet, 2 were living outside Alberta, and one individual was not diagnosed with cancer). 54 declined participation (with the majority stating they were not interested in the intervention, while 10 stated they were effectively managing stress through other methods. 5 asked to be contacted later or considered for the program at a later date. 57 participants have been enrolled thus far in the program: 2 withdrew (1 MBCR, 1 wait-list). Reasons for discontinuing with the study included treatment related issues and schedule change. 47 have completed the program or in the process of completing the study. No adverse events have been reported. Final analysis of the data is not yet available to compare the intervention and control groups; however, several preliminary comments and conclusions can be made from the experience of the trial to-date.

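### Between T1 and T2, adverse events are sought on a weekly schedule in the MBCR arm but only through a standing request in the wait-list arm, so event counts by arm are not comparable

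*Protocol article*

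**What the plan says.** The Adverse events section of the protocol article gives four ways for an event to reach the study team:

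- The log: "All participants are requested to record and disclose any adverse events in their homework logs".
- The instructor, who asks about participants' "weekly experiences at each class session".
- A reporting request, in the same sentence as the log: "and to report them to the group instructor or the research coordinators".
- An open invitation: "Participants are welcomed and strongly encouraged to contact research staff to discuss any questions or events they consider problematic".

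The section Meditation Log and attendance describes the log: "Information on minutes spent in home practice of meditation and yoga is collected from each participant each week and returned to the study coordinator". Table 1, under Outcome measures and questionnaires, lists it as a measure of dose ("Delivered: Attendance log Received: Meditation Log"), administered during the intervention.

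Under Screening, consent and enrollment, wait-list participants are told their start date and "contacted closer to such date to send course materials". Under Treatment as Usual (TAU) wait-list control condition, they complete T1 and T2 around the wait, then take the programme and complete T3.

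The Discussion states: "No adverse events have been reported". It does not split this by arm, period or route of collection.

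**The concern.** The adverse-event rule is addressed to everyone randomized, but its two scheduled routes depend on being in the programme. If only one arm is asked regularly, the number of events recorded depends on the asking as well as on the events. A higher count under MBCR could then reflect nothing more than more frequent inquiry. Background events in waiting participants, some of whom may be in active cancer treatment under the eligibility criteria, would be recorded less completely.

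T1–T2 is the only period in which the two arms are concurrent and randomized. It is therefore the only period in which an excess of events could be attributed to MBCR without an outside comparator.

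**Working it through.** The plan gives no figure to reproduce and no formula applies. The check sets each collection route against what each arm receives between T1 and T2.

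**Inputs**

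- Classes: 8 weekly sessions in the MBCR arm (Intervention group section).
- Log: returned weekly, recording home-practice minutes and shared with the group instructor (Meditation Log and attendance); timed to the intervention in Table 1.
- Wait-list contacts during the wait: the T1 and T2 questionnaires (TAU wait-list section). Course materials arrive near the participant's own start date (Screening, consent and enrollment).
- Planned size: 32 per arm, 64 in total (Analysis of power for primary effects).

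**Routes available between T1 and T2**

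| Route | MBCR arm | Wait-list arm |
|---|---|---|
| Instructor's inquiry at class | 8 (1 per class × 8 classes) | 0 |
| Weekly log | weekly over the 8 weeks | 0 |
| Request to report to coordinators | open | open |
| Invitation to contact research staff | open | open |
| Adverse-event item at T2 | none listed in Table 1 | none listed in Table 1 |

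**Step 1. Does the log reach waiting participants?** No sentence says outright that it does not, so this is an inference. It rests on three points. The log records home practice, which waiting participants have not been taught. Table 1 times the log to the intervention, whereas the POMS, C-SOSI, PTGI-R, FFMQ and FACIT-Sp rows are expressly timed for either MBCR or the wait; the authors marked collection during the wait where they intended it. Wait-list participants receive course materials only as their own start approaches. I take the homework log to be the Meditation Log of Table 1, as the article describes no other.

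**Step 2. Does the class inquiry reach them?** No. The control group enters the classes after the wait, by which time the randomized comparison has ended.

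**Step 3. What remains?** Two routes are common to both arms, and both require the participant to take the initiative. For 32 of the 64 planned participants (half) these are the only stated routes in the controlled period.

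**Step 4. What does the reported zero rest on?** It pools MBCR participants under scheduled inquiry, waiting participants under the standing request, and any wait-list participants who have since entered the programme. The article gives no split, so the wait-period contribution cannot be separated.

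**The case against.** Several points on the other side are sound and limit the finding.

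- *Waiting participants do have a route.* The sentence that mentions logs also asks for reports to coordinators, and contact with staff is encouraged. Controls later take the programme and can then keep logs. A reader might infer that events in the wait-list arm go uncollected, or that the rule cannot be followed for half the sample. The text does not support either reading. The difference is scheduled against participant-initiated collection.
- *The active side is modest.* The instructor asks about the week in general; no structured adverse-event question is specified. The 8 inquiries are occasions for disclosure, not 8 formal assessments.
- *Worsening distress is measured equally.* A reader might infer that deterioration in distressed waiting participants would be missed. It would not: POMS and C-SOSI are completed at T1 and T2 in both arms, and the Study design section counts symptom deterioration among the things the wait-list controls for.
- *No planned analysis compares events between arms.* The objectives, hypotheses and analysis sections contain no such test, and the Discussion's statement makes no comparative safety claim. Any bias in a comparison would tend to make MBCR look worse, not hide its harms.
- *This is a condensed article.* A fuller protocol might contain an adverse-event item at T2.

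The last point does not dispose of the matter. The article does not merely leave a detail out; it states a collection method which, followed as written, gives unequal ascertainment by arm. The absence of a planned test reduces the consequence, but any listing of events by arm would still invite a comparison the data cannot support.

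**Conclusion.** The point holds for discrete adverse events in the randomized T1–T2 period. The MBCR arm has 8 class inquiries and a weekly log; the wait-list arm has no scheduled prompt and relies on a standing request. Counts by arm are not comparable, and the reported zero is weaker evidence for the wait-list arm than for the MBCR arm. The article gives no capture rates, so the size of any distortion in counts cannot be estimated.

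This rests on the inference that waiting participants keep no log, and on the article's account of data collection being complete as regards routes.

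It would go too far to say that the controlled period is of no use for safety. Symptom worsening on POMS and C-SOSI remains a fair between-arm comparison; only event counts are affected. The feasibility objective and the efficacy analyses are untouched. The change is worth making because it is cheap, but it does not threaten the trial's main conclusions.

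**What to change.** 1. Add one adverse-event question, with identical wording and recall period, to the T2 online battery in both arms, and to T3 in the wait-list arm.
2. Tabulate T1–T2 events by arm from that item only.
3. Report events from logs and instructors separately, labelled as a programme-period source.
4. Amend the Adverse events section to say which routes apply during the wait, and attach arm, period and route to any statement that no events were reported.

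The cost is a slightly longer questionnaire, a minor ethics notification and some additional reports to review.

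The main limit is timing. The Discussion gives 57 enrolled, leaving 64 − 57 = 7 to reach the target, and 47 who had completed or were completing. It does not say how many had passed T2, but the new item cannot supply T1–T2 data for those who had. For them, the report should state that events were collected mainly during the programme and are not compared between arms. The by-arm table should give as its denominator only those who were asked the question.
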